### Sample size

Ensuring an adequate sample size will allow for more accurate estimation of regression coefficients and reduce the potential for overfitting. Rules of thumb for calculating required sample size for prediction models with binary outcomes (such as ten events per candidate predictor parameter (EPP)) are now considered too simplistic to provide robust estimates of minimum required sample size [50]. The actual required sample size is context-dependent and is informed by several factors. We used the *pmsampsize* package in Stata (available online: https://riskcalc.org/pmsamplesize/) to calculate our required minimum sample size [51].

The Cox-Snell R^2^ is a measure of overall model fit and based on the method of Riley et al. [51] an anticipated Cox-Snell R^2^ must be specified when calculating sample size, usually based on previous studies of similar patient groups/outcomes. No previous prognostic model study predicting relapse of depression identified so far has reported a Cox-Snell R^2^ and so, to ensure an adequate minimum sample size, we used the recommended conservative estimated Nagelkerke R^2^ of 15% [52]. This corresponds to a Cox-Snell R^2^ of 0.0945, assuming an overall outcome proportion of 0.2, which again is a conservative estimate based on the literature [3]. We targeted an expected shrinkage factor (*S*) of 0.9 (to reflect small optimism in predictor effect estimates), as recommended [52].

To include all predictors, we require 8 predictor parameters (*P*), which corresponds to PHQ-9 score at remission, previous depressive episodes, co-morbid anxiety, severity of index episode and RCT Intervention (including 2 parameters for each continuous predictor to account for potential non-linear trends). Therefore, our minimum required sample size (*n*) is 722 (with 145 events) for these predictors. Our actual sample size exceeds this, and therefore, we anticipate that the study will be of a sufficient size to require minimal shrinkage and provide meaningful estimates of predictive performance.

### Missing data

To avoid loss of power and precision, missing data will be handled using multiple imputation with chained equations (MICE) [53]. Missing values will be imputed based on other predictor and outcome values, under a missing at random assumption, and multiple copies of the dataset will be created with identical known information and different imputed values, reflecting the uncertainty associated with imputation. Imputation will be undertaken for each RCT separately, to preserve the clustering of participants within trials and any between-trial heterogeneity in predictor effects and outcome prevalence. We will assume that data are missing at random, unless this appears inappropriate upon inspection and discussion with original trialists. We will use the percentage of participants with one or more missing values to determine the number of imputations needed, in line with current guidance; at least 20, as long as this is greater than or equal to the percentage of participants with one or more missing values [19, 54]. Results from non-imputed and imputed data will be compared as a form of sensitivity analysis. Given the selection criteria, we do not anticipate any systematically missing predictors across datasets.

### Statistical analysis methods

#### Data pre-processing

The datasets will be combined and harmonised to ensure consistency across trials. To assess IPD integrity, we will compare numbers of participants in each treatment arm with those reported in the primary references. We will check the relapse rate within each arm and compare these across datasets. To define the quality of the IPD for prognostic modelling, we will perform risk of bias assessment on the included datasets using the PROBAST [55]. Only the participants, predictors and outcome domains are pertinent; the analysis domain is used for assessment of prognostic model development and validation studies which do not apply to the RCTs included in this study.

Once remission has been identified this will represent time t=0. Relapse will then be coded as 0=no relapse, 1=relapse as described in “End-point” section. Descriptive statistics will be produced for all predictors and outcome data. Exploratory univariable analysis will be performed to evaluate the unadjusted relationship between each predictor variable and the outcome variable, but not for the purpose of informing predictor selection. We will explore percentage of cases that relapse over the different studies to assess comparability of data sources.

#### Model development

The model will be developed using a multilevel multivariable logistic regression, with a binary (relapse/no relapse) outcome. Model parameters will be estimated via unpenalised maximum likelihood estimation and then penalised post-estimation using a uniform shrinkage factor (see later). The modelling will preserve the clustering of patients within trials, by having a random effect on the intercept, a random intervention effect and a random control effect, also allowing for between-study correlation in these pair of effects. If it is not possible to fit random effects in the multilevel logistic regression model, as originally planned, we will explore alternative modelling approaches. This would initially consist of a Generalised Estimating Equation model to control for the clustering without a random intercept. If this is also not possible, we will perform a single-level analysis with robust standard errors and accept that the limitation is that there may be a clustering effect that we are unable to properly control for.

Stepwise methods for predictor selection are not generally recommended for prediction models as this has been reported to remove judgment of the analyst from the process of model development as well as leading to *estimation bias* (estimating the performance of a prediction model after testing for statistical significance of predictors in the same data) [36]. We have selected our key predictors on the grounds of best available evidence and clinical acceptability, as well as practical reasons related to data availability. The list of predictors is felt to be of appropriate length, so we will avoid predictor selection techniques during model development and include all predictors regardless of their statistical significance (“full model” approach) [56]. This will also apply in the presence of multi-collinearity, which is not an issue for prediction purposes. We will only consider the need to exclude predictors due to collinearity if this is preventing convergence of the estimated model.

The full model approach described has the advantage of not being overly data-dependent and avoids the risk of removing clinically important predictors from the final model [56]. Calibration plots with loess smoothed calibration curves will be provided. Optimism will be measured and adjusted for using bootstrapping.

We will explore non-linear relationships in the modelling process using multivariable fractional polynomials (MFPs), a flexible and recommended approach for modelling continuous predictors in medical datasets. The other recommended method for modelling continuous predictors is the use of restricted cubic splines, and while these two methods often result in similar models, there is some evidence that MFPs perform better than restricted cubic splines in the presence of simpler relationships and medium amounts of information, as is the case here [20, 57]. We have factored in two predictor parameters (beta coefficients) per continuous variable to account for this approach, as described in the “Sample size” section.

Beyond the primary analysis outlined, and dependent on final sample size, an exploratory analysis will be performed investigating the role of less established relapse predictors (Table 3). Univariable associations between these predictors and outcome will be explored and, because the role of these variables as relapse predictors is less well understood, predictor selection through stepwise backward elimination will be used to develop an exploratory model. With sufficient sample size, stepwise backward elimination is an acceptable form of variable selection, performs similarly to other predictor selection approaches (for example, LASSO [58]) and is more compatible with our planned approaches for handling missing data and exploring non-linear trends. Guidance suggests using a more liberal p-value than the standard 0.05 for retention [19]; we will use a p-value of 0.157 or less as a stopping rule (consistent with Akaike information criteria (AIC) at one degree of freedom) [59].

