### RCT intervention

Because the data are drawn from RCTs, we must be mindful of the fact that approximately half of the participants have received a treatment (above usual care) and the other half have not. Where the treatments were found to be effective, not modelling the effect of different treatments can lead to unreliable risk predictions when the model is validated in a different population. Excluding the treated individuals would mean losing half of the available data, and so a preferable option is to explicitly model for treatment effect when developing a prognostic model [41, 42]. The treatments in all RCTs were acute-phase psychological treatments rather than relapse prevention interventions, and therefore, we do not know what their effect on relapse outcomes were. One of the studies [31] did include an element of relapse prevention beyond the acute phase treatment (advisors phoned the patients every 2 months to check how they were getting on and encourage them to keep following the intervention advice). The interventions are also heterogeneous, and so it is possible that they affected relapse outcomes in different ways. To avoid overcomplicating the model, we will code the presence or absence of an effective intervention as a dichotomous variable. We will define an effective intervention by whether individual participants entered remission after receiving an RCT intervention (code=1) or whether they entered remission after receiving a control (code=0).

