Further limitations relate to measurement of start-point (remission) and end-point (relapse or not), which will be measured using PHQ-9 score. The gold standard would have been to use diagnostic interviews, which may have been possible with a prospective cohort study. The PHQ-9 is a validated and widely used tool with good sensitivity and specificity [65], and the large sample size (possible because of the use of secondary data analysis) should compensate for this. A further point to consider is that the start- and end-points are defined at the next time-point they were actually measured rather than necessarily capturing the precise “real-world” moment of remission. However, this reflects the situation in general practice, where diagnostic tools will be applied at patient consultation rather than in real time. Therefore, we feel this is justifiable and actually mirrors the clinical picture accurately. We will use the reliable clinical recovery and deterioration definitions (sample size allowing) to ensure robust coding of start- and end-points.

In the event that multilevel modelling with a random intercept and random effects on the intervention/control variable is not possible, we will be required to make an assumption that the effects of the different interventions and controls in the RCTs were homogenous. It is not likely that the interventions had a significant effect on relapse rates, even where they did improve acute depression symptoms. However, it is possible that one or more of the interventions (or controls) did exert an effect on relapse of which we are not aware. We will take a pragmatic approach to modelling this, following the steps that we have outlined in the “Methods” section. A further limitation is that the data we plan to analyse do not allow for survival analysis, as the follow-up time-points were insufficiently similar and infrequent. However, time to relapse is important and would increase our understanding; future prospective work should consider this when designing strategies for data collection.

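### The primary multilevel model lists three study-level random effects where one binary arm variable supports only two, and the fallback skips the random-intercept-only model

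*Protocol article*

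**What the plan says.** The Model development section describes a multilevel logistic regression that keeps patients clustered within studies "by having a random effect on the intercept, a random intervention effect and a random control effect". That is three random terms. The same sentence then turns to correlation and refers to a pair: "also allowing for between-study correlation in these pair of effects".

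The RCT intervention section fixes how arm enters the model: "we will code the presence or absence of an effective intervention as a dichotomous variable". Table 2 gives the codes as 0 for remission after control and 1 for remission after intervention.

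The fallback is also set out in Model development. "If it is not possible to fit random effects in the multilevel logistic regression model, as originally planned, we will explore alternative modelling approaches". The first step is then named: "This would initially consist of a Generalised Estimating Equation model to control for the clustering without a random intercept". If that fails too, "we will perform a single-level analysis with robust standard errors".

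Limitations restates the primary model in different terms, referring to the event that "multilevel modelling with a random intercept and random effects on the intervention/control variable is not possible". It adds that in that case "we will be required to make an assumption that the effects of the different interventions and controls in the RCTs were homogenous".

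**The concern.** With one binary arm variable, a random intercept, a random intervention effect and a random control effect are linearly dependent within a study. The data carry information on two study-level quantities, the control-arm and intervention-arm log-odds of relapse. A third random term with correlation adds parameters that no amount of data can separate.

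This concerns the primary model, and the model is fitted many times. It is refitted in each of hundreds of bootstrap samples, with imputation inside each, and in each internal-external cross-validation cycle. A redundant variance parameter goes into every one of those fits.

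If the fit fails, the plan moves to models without a study-level intercept. Elsewhere the plan takes care to keep study differences: imputation is done trial by trial so that heterogeneity in outcome prevalence survives. The fallback would give up study-specific baseline risk, possibly because of how the random effects were written down rather than because the data cannot support them.

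**Working it through.** **The plan's own figure.** The only planning figure tied to this model is the minimum sample size. The inputs come from the Sample size section: P = 8 parameters, target shrinkage S = 0.9, Cox-Snell R² = 0.0945, outcome proportion 0.2.

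- n = P / [(S − 1) × ln(1 − R²/S)] = 8 / [(−0.1) × ln(1 − 0.105)] = 721.2, rounded up to 722.
- Events: 722 × 0.2 = 144.4, rounded up to 145.

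Both figures reproduce and are not in dispute.

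**Number of random quantities.** Let u0, u1 and u2 be a study's random intercept, intervention effect and control effect. With arm coded 0/1, the study's random contributions are:

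- intervention arm: u0 + u1
- control arm: u0 + u2

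The design matrix for (u0, u1, u2) has rows (1, 1, 0) and (1, 0, 1). Its rank is 2, for three random effects.

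**Number of identifiable terms.** Write V0, V1 and V2 for the variances and C12 for the covariance of u1 and u2, with u0 independent of the pair. This is the closest literal reading of the sentence. The observable moments are:

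- Var(intervention) = V0 + V1
- Var(control) = V0 + V2
- Cov(intervention, control) = V0 + C12

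Rank of the map from parameters to these three moments, by specification:

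| Random-effects specification | Parameters | Rank | Identified |
|---|---|---|---|
| Intercept independent of a correlated intervention/control pair | 4 | 3 | No |
| All three with unstructured covariance | 6 | 3 | No |
| All three mutually independent | 3 | 3 | Yes, but excluded by the stated correlation |
| Intercept plus one correlated arm coefficient | 3 | 3 | Yes |
| Two correlated arm effects, no separate intercept | 3 | 3 | Yes |

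**Illustration.** The values below are chosen only to show the point. Take (V0, V1, V2, C12) as (0, 0.3, 0.3, 0.2), (0.1, 0.2, 0.2, 0.1), (0.2, 0.1, 0.1, 0) or (0.25, 0.05, 0.05, −0.05). All four are valid covariance structures. Each gives variances of 0.3 and a covariance of 0.2 for the two arms, hence the same likelihood. The data cannot choose among them.

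**What is and is not affected.** The likelihood depends on the random effects only through those three moments. The fixed effects are therefore still estimable. What is arbitrary is how variance is split among the three random terms.

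**The fallback, step by step.** The GEE allows for within-study correlation but has no study-specific intercept. The single-level model has none either. Robust standard errors change the standard errors of that model but none of its coefficients, so every predicted risk is the same as without them. Neither a random-intercept-only model nor any other reduced random-effects model is named in between.

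**Support for the random effects.** Table 1 lists eight sources. COBRA compares two active treatments and WYLOW has no trial intervention. At most six sources can therefore inform a within-study intervention-versus-control contrast, so even the identified model has few clusters to work with.

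**The case against.** The strongest reply is that this is loose wording around a sound model. The word pair in Model development points to two effects. The phrase in Limitations can be read as an intercept plus one arm coefficient, which is identified. That may well be what was meant. It does not settle the matter, because the operative Methods sentence names three terms and does not say which two form the pair.

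Mitigations also stand. Relapse percentages are compared across studies, calibration is checked and the intercept updated, and internal-external cross-validation estimates heterogeneity in performance. Differences between studies would be examined even under the fallback. None of this repairs the specification.

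Four stronger readings are tempting but not supported:

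- **That the fit will probably fail.** Software may fail, return arbitrary variance components or drop a redundant term. Failure is possible but not shown to be likely. The promise to explore alternatives also leaves some room, although the GEE is named as the first step.
- **That the fallback would bias coefficients by a calculable amount.** A reader could use 1/√(1 + 0.346τ²), where τ is an assumed between-study SD on the log-odds scale. For τ from 0.2 to 0.8, marginal coefficients are about 0.99 to 0.90 of study-specific ones. That is a difference of scale between two estimands. It is not bias, and it does not measure between-study differences leaking into predictor effects.
- **That the homogeneity sentence in Limitations is untrue.** It describes the plan's own fallback, where a single dichotomous coefficient does assume a common effect. A random-intercept-only model with a fixed intervention effect makes the same assumption.
- **That the GEE should go.** It accounts for within-study correlation, and population-averaged predictions are defensible for a patient outside the eight studies. Removing it is a preference.

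**Conclusion.** The point holds as a specification error with an incomplete fallback. As written, the random-effects covariance has at least 4 parameters against 3 identifiable terms, and 6 against 3 if unstructured. This follows from the 0/1 arm coding and the stated correlation, and needs no assumption about the data. The description is also inconsistent within Model development and between that section and Limitations.

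The consequence is limited. Estimation of the fixed effects is not undermined by the redundancy itself. The risk is that non-convergence or uninterpretable variance components send the analysis to a fallback that loses study-specific baseline risk, when a simpler random-effects model would have kept it. How likely this is, and how much predictions would change, cannot be determined from the document.

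**What to change.** 1. In Model development, replace the three random terms with a random study intercept plus one random coefficient for the 0/1 arm variable, correlated. Two correlated arm-specific effects with no separate random intercept is an equivalent form. Either has three covariance parameters, all identified.
2. Use the same description in Limitations, so that both sections refer to one model.
3. Insert a random-intercept-only model with a fixed intervention effect as the first fallback. The GEE and single-level model can stay after it.
4. State that robust standard errors in the last step do not alter predicted risks.

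The cost is wording only, and the primary model has fewer variance parameters to fit. These changes leave the eight predictor parameters as they are, so the minimum of 722 participants and 145 events stands. Fixed study intercepts would also keep baseline risk, but they are not needed here. If their seven extra terms were all counted as parameters (the most demanding reading), P = 15 gives 15 / [(−0.1) × ln(1 − 0.105)] = 1352.2, or 1353 participants.

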#### Internal validation

The predictive performance and optimism of the developed model will be assessed. Calibration (a measure of the agreement between predictions from the model and observed outcomes) will be assessed by plotting observed vs predicted risks for groups defined by tenths of individual predicted risk (calibration plot) and by including a loess smoothed calibration curve across individuals (avoiding grouping). Apparent and optimism-adjusted calibration-in-the-large and calibration slope will be estimated. Discrimination (the ability of the model to differentiate between those who do or do not relapse) will be assessed using the C (concordance) index. The C-index assesses the extent to which the model assigns a higher probability of relapse to a patient who did eventually relapse in contrast to a patient who did not. The optimism-adjusted C-index will be derived using bootstrapping.

Optimism describes the risk of obtaining misleading measures of predictive accuracy when this is assessed in the same dataset used for model development, mainly due to overfitting. Internal validation can be used to provide optimism-corrected performance statistics can mitigate for this effect. Non-parametric bootstrapping will be used as a means of resampling the original dataset. This has the advantage, for example over a single split-sample approach, of allowing all of the data to be used in model development. Bootstrapping will be performed within each individual study, and then, these will be combined to create a new bootstrap sample to ensure studies are represented evenly for the final analysis. Multiple imputations for missing data will be performed within each bootstrap sample.

A bootstrap sample will be created in which the model development process will be repeated. The performance of this model will be evaluated in the bootstrap sample (bootstrap, or apparent, performance) and in the original sample (test performance). This process will be repeated hundreds of times and the average difference between the bootstrap and test performance for each performance statistic provides the estimate of optimism for that statistic. Optimism-adjusted performance statistics will be derived by subtracting the average optimism estimate (from bootstrapping) from the apparent performance *of the original model*. The uniform shrinkage factor (calculated as the optimism-adjusted calibration slope) will then be applied to all estimated predictor effects to produce a penalised logistic regression model, and the intercept updated to ensure calibration-in-the-large.

Sensitivity, specificity and positive and negative predictive values for the model will be calculated at risk thresholds considered potentially clinically relevant. It is unclear whether the creation of risk groups is in the best interests of patients, but they are often used to guide clinical decision making [21]. In the absence of a gold standard test (as is the case here), the need for and definition of risk groups will be determined based on discussion within the research team and through consultation with our PPI group during model development. We will avoid basing risk thresholds on the data used to develop the model. The net benefit of the model at particular thresholds will also be examined using decision curve analysis and compared to treat all and treat none decisions [60].

